### 3.6.3 Drug management

Sintilimab injection should be stored in the original package with the vial under refrigeration at 2~8°C, protected from light, avoiding refrigeration and shock, with an expiration date of 24 months. Anlotinib hydrochloride capsule should be kept under light shielding, airtight, and below 25°C, with an expiration date of 18 months.

### 3.6.4 Treatment prescription

Treatment prescription was prescribed by the patient's physician, and patients suitable for this study were selected for voluntary enrollment based on the enrollment criteria.

## 3.7 Duration of research

The study is expected to last 5 years, including a 12-month enrollment period. After discontinuation of treatment, each patient will be followed-up until death or withdrawal from the study.

- Planned date for 1st patient enrollment/trial start: June 10, 2021
- Planned date for the last patient enrollment: June 10, 2023
- Planned date for the last patient to be disenrolled/end of trial: October 10, 2023 (4 months after enrollment of last eligible patient)
- Expected report date: December 30, 2023

## **4. Research procedures and data collection**

### **4.1 Data collection program**

The duration of safety data collection spans from the time the patient signs the Informed Consent Form (ICF) until 30 days after the final dose. All adverse events must be documented in the Case Report Form (CRF) from the moment the ICF is signed until the study concludes. The incidence and severity of adverse events will be observed and assessed according to the NCI-CTCAE 5.0 criteria. Each patient will undergo scheduled visits, and specific data will be recorded at various time points during these visits.

### **4.2 Screening phase**

The screening period for this study will be completed within 28 days. During this time, additional study visits may be included due to variations in study procedures. At the screening visit, patients will be asked to read and sign the informed consent form before undergoing any procedures related to the study that are not part of standard care. As research subjects, patients have the right to be fully informed about the study and may request the doctors to explain or clarify any part of the informed consent form that they do not understand. The study staff will perform the following tests and procedures to confirm the patient's eligibility to participate in this study:

- 1) Review patients' medical history;
- 2) Review of medications the patients are currently taking and have taken in the past, including herbal medications;
- 3) Have a physical exam that includes testing height, weight, body surface area (BSA) and vital signs (temperature, blood pressure, respiration, and heart rate), pulse,

oxygen saturation by oximeter, and pulmonary function tests. An electrocardiogram (ECG) will be performed prior to the start of study treatment;

4) The patients will be asked about symptoms related to the disease (performance status) that they are suffering from;

5) Imaging:

Positron emission tomography/computed tomography (PET/CT) scans will be conducted from the base of the skull to the upper thighs. During this procedure, patients will be injected with a radioactive tracer that is absorbed by cancer cells, allowing for their detection by the PET scanner. Additionally, computed tomography (CT) will be used to image the internal structures of the body. CT scans and magnetic resonance imaging (MRI) will be performed on areas of known disease.

6) Sample collections:

A blood sample (approximately 20 mL) will be collected for laboratory testing. This will include assessments of blood chemistry, kidney and liver function, as well as counts of red blood cells, white blood cells, and platelets. Thyroid function will also be tested, and patients will be screened for Hepatitis B Virus (HBV) and Hepatitis C Virus (HCV) infections. Patients wishing to participate in the study must be free of known HIV infection and must test negative for HBV and HCV or have an HBV viral load of  $\leq 2000$  IU. For female subjects of childbearing potential, a urine or blood sample will be required for a pregnancy test. Additionally, a sample of tumor tissue will be tested for PD-L1 expression. If no tumor tissue is available, the patient will be asked to undergo a tumor tissue biopsy for a more precise assessment. At least 10 tissue sections will be needed.

7) Sample testing

Doctors may decide to test tumor tissue samples for ROS1 or ALK gene mutations. PD-L1 Testing: Part of this study involves evaluating whether patients with a specific biomarker are likely to respond to the study treatment. During the screening process, biomarker testing will be conducted to identify certain genes, which will enable the study doctor and clinical team to determine the patient's eligibility for participation. This biomarker testing may also provide valuable information to help guide research decisions based on the genetic profile of the participant's disease.

### **4.3 Preoperative treatment period**

Sintilimab (200mg fixed dose) iv, d1, q3w + anlotinib 10mg, po, qd1-14, q3w + platinum-doublet chemotherapy, evaluated after 3 cycles of combination therapy and discontinued for 3 weeks (21 days) followed by surgery, which was performed within 4-6 weeks (22-42 days) of the last dose. The time between each study dosing treatment was called a cycle.

#### **4.4 Radical surgery**

Within 4-6 weeks (22-42 days) of the last dose, the radical surgery was performed.

#### **4.5 Follow-up period**

After completing the pre-surgical treatment, patients will enter a follow-up period. During this time, doctors will continue to evaluate the patients' health. It is crucial to monitor their health status, including recovery progress, potential disease progression, and any serious adverse events. Patients may undergo surgery to remove tumor tissues during this period. Some of the tumor samples will be analyzed to assess how much of the tumor remains and to test for the same or similar biomarkers that were evaluated during the screening phase.

##### Initial follow-up (1st and 2nd follow-up)

The first follow-up visit will take place in the hospital approximately one month after the completion of pre-surgical treatment, and it will occur before or on the day of the lumpectomy. Surgery is scheduled to be performed within 4-6 weeks after finishing pre-surgical treatment. Prior to surgery, a contrast-enhanced PET/CT or CT scan will be conducted, and the results of pulmonary function tests will be reassessed. A second follow-up visit will occur approximately two months after the first follow-up visit and after the patient has undergone surgery. Procedures performed and samples collected during the study drug administration may be repeated one or more times during these two follow-up visits. Following the initial follow-up visit and surgery, patients will receive adjuvant therapy with sintilimab for up to 13 cycles as part of their standard care.

#### **4.6 Additional follow-up**

After surgery, patients will have additional follow-up visits approximately every three months, with the possibility of more frequent check-ins. These follow-up visits

can be conducted over the phone or in the hospital. Patients will receive evaluations every three months for a total of two years, followed by visits every six months thereafter. As part of the follow-up, patients will undergo a CT or MRI scan of the lesion site or areas of potential spread every three months for the first two years. This will continue every six months for the next three years and then annually for a total of five years, until tumor recurrence or death occurs.

#### **4.7 Survival visit**

After surgery, follow-up visits will be conducted every three months for the first two years, followed by visits every six months for an additional three years. Follow-up care includes, but is not limited to, performing CT or MRI scans of the lesion site or areas of potential spread until tumor recurrence or death occurs. During follow-up, the following parameters will be closely monitored and recorded: time to disease progression, time of death (with options for telephone follow-up and record-keeping), and any other therapeutic agents or treatments administered.

#### **4.8 Adverse event follow-up**

After the last dose, follow-up will continue to monitor for any new adverse events (AEs). For AEs that do not resolve after discontinuation of the drug, monitoring will continue until the adverse event is resolved, returns to baseline levels, or is deemed clinically insignificant.

#### **4.9 Handling steps for patient withdrawal from follow-up program**

Patients have the right to withdraw informed consent at any time and for any reason. If a patient agrees to participate in survival follow-up, they will not be considered to have withdrawn from the study. However, if they choose not to participate in survival follow-up, they will be considered withdrawn. Therefore, investigators should make every effort to regularly contact patients to assess their health status, including at least their survival status.

### **5. Statistical methods**

#### **5.1 Analysis variables**

##### **5.1.1 Main indicators**

1) Pathologic complete response (pCR) rate: The pCR rate is defined as the proportion of subjects with no residual invasive cancer on hematoxylin and eosin-stained slides of resected lung specimens and lymph nodes after completion of neoadjuvant therapy. For pathological assessments, primary lung tumors and lymph node specimens were staged using the AJCC criteria (8th edition). Residual viable tumor percentage in primary tumors was determined from routine hematoxylin and eosin-stained specimens. Tumors with no residual tumor cells (ypT0N0M0) were classified as having pCR. Pathological downstaging was defined as a reduction in ypTNM stage post-treatment, with no new lesions or progression of existing lesions.

## 2) Safety

- Incidence of treatment-related adverse events (TRAE);
- Incidence of AEs that resulted in treatment discontinuation and/or early study withdrawal;
- Incidence of SAEs and drug-related SAEs;
- Incidence of deaths;
- Discontinuation of medication for adverse event reasons;
- Changes in vital signs before and after treatment (heart rate, blood pressure, temperature, respiration);
- Changes in whole body physical examination before and after treatment;
- Abnormalities in clinical laboratory tests.

### 5.1.2 Other indicators

- Major pathologic response (MPR) rate, defined as the proportion of subjects with  $\leq 10\%$  surviving tumor cells in the resected primary tumor and all resected lymph nodes. For pathological assessments, primary lung tumors and lymph node specimens were staged using the AJCC criteria (8th edition). Residual viable tumor percentage in primary tumors was determined from routine hematoxylin and eosin-stained specimens. Tumors with  $\leq 10\%$  viable cells were classified as having MPR. Pathological downstaging was defined as a reduction in ypTNM stage post-treatment, with no new lesions or progression of existing lesions.

- Event-free survival (EFS), defined as the interval from enrolment to the

earliest occurrence of local progression resulting in inoperability; unresectable tumour, disease progression or recurrence according to RECIST version 1.1 as assessed by the investigator; or death from any cause. Progression-free survival was treated as censored on the date of the last validated tumor assessment for subjects in whom no tumor progression or death was observed.

- Overall survival (OS), defined as the time from study entry (i.e., after signing ICF) to death from any cause. Subjects who were alive at the time of last contact had their overall survival censored at the date of last contact.

- Patients underwent radiological evaluations by investigators according to RECIST version 1.1 at baseline, after two cycles of neoadjuvant therapy, prior to surgical resection, and every 4 cycles during adjuvant therapy until disease progression, intolerable toxicity, death, or withdrawal of consent. Complete and partial responses were confirmed radiologically at least 4 weeks later, while stable disease was confirmed at least 8 weeks after the initial assessment. The ORR was defined as the proportion of patients achieving either a complete or partial response. Patients were followed up by visits or phone calls every 12 weeks to determine survival status.

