#### **3.3 Secondary endpoints**

Observe the postoperative major pathologic response (MPR) rate, event-free survival (EFS) and overall survival (OS).

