### 3.6.2 Dose adjustment and discontinuation of administration

Anlotinib was discontinued if patients developed haemoptysis. For other grade  $\geq 3$  treatment-related adverse events (TRAEs), anlotinib was reduced to 8 mg, and the dose of chemotherapy was reduced by 25.0% of the last dose. Dose modification of sintilimab was prohibited. Patients experiencing intolerable adverse events that led to a delay or discontinuation of one drug continued treatment with the remaining study drug. Treatment continued until intolerable toxicity occurred or consent was withdrawn. Those who developed progressive disease were permitted to undergo surgery or receive SOC-CRT at the investigator's discretion.

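### The only censoring rule given for EFS names progression-free survival and omits unresectable tumour, so a listed EFS event can be censored or dated late

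*Protocol*

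**What the plan says.** Section 3.3 names three secondary endpoints: MPR rate, EFS and OS. Progression-free survival is not among them and is defined nowhere in the protocol.

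The EFS item in section 5.1.2 starts the clock at enrolment and counts whichever of its events comes first: "local progression resulting in inoperability; unresectable tumour, disease progression or recurrence according to RECIST version 1.1". Assessment is by the investigator, and death from any cause is the last alternative.

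The sentence that follows, inside the same item, is worded for progression-free survival. Under it, the endpoint is "censored on the date of the last validated tumor assessment for subjects in whom no tumor progression or death was observed". No other censoring rule is given for EFS. The OS item has its own rule (last contact).

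On what happens after progression, section 3.6.2 leaves the choice to the investigator: "Those who developed progressive disease were permitted to undergo surgery or receive SOC-CRT". Section 3.6.1 also allows surgery after imaging-confirmed progression, under conditions and with the principal investigator's consent.

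**The concern.** The event list and the censoring rule should divide patients cleanly: anyone with a listed event is an event, and everyone else is censored. Here they do not. Unresectable tumour is in the list, but it is not among the things that prevent censoring. The rule also carries the name of a different endpoint, so a programmer must either conclude that EFS has no censoring rule or apply one that disagrees with the definition two lines above it.

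The patients affected are pre-operative treatment failures without measured progression. EFS in a neoadjuvant trial is meant to count such failures, so a rule that censors them, or moves their event date later, makes the curve look better than the definition allows.

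**Working it through.** The protocol states no EFS event count, target, test or power; the calculation in section 5.3 is for pCR only. There is therefore no EFS figure to reproduce. The check is to take each type of patient through both sentences, then to show the possible scale.

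**Step 1. Event list against censoring sentence (both section 5.1.2), with the sentence applied to EFS**

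| Patient | Event list | Censoring sentence | Agree? |
|---|---|---|---|
| (a) Tumour unresectable, no RECIST progression, alive | Event when unresectability is established | Censored at last tumour assessment | No |
| (b) RECIST progression before surgery, then resected | Event at progression | Not censored: progression observed | Yes |
| (c) Local progression causing inoperability | Event | Not censored: progression observed | Yes |
| (d) Death | Event | Not censored | Yes |

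Only row (a) conflicts. If such a patient later progresses or dies and this is observed, the censoring sentence no longer applies. The patient is then an event, but at the later date rather than when unresectability was established.

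**Step 2. Whether the conflict can be read away**

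The punctuation leaves it unclear whether the RECIST qualifier also governs unresectable tumour. That reading would give the term little meaning, because the protocol's own tumour assessment form offers only CR, PR, SD, PD and NE as overall outcomes. Taking the censoring sentence literally as a rule for progression-free survival removes the contradiction, but then EFS has no censoring rule and the sentence governs an endpoint the trial does not have. The text needs correcting on either reading.

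**Step 3. Scale (illustration only)**

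Inputs: n = 45 (planned enrolment, sections 3.4 and 5.3). k, the number of patients of type (a), is an assumption; the protocol gives no rate. All 45 are taken to be at risk when the k patients fail.

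Kaplan-Meier factor when the k patients are coded as events: (45 − k)/45. Factor when they are censored: 1. Difference just after surgery: k/45.

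- k = 1: 1/45 = 2.2 points
- k = 3: 3/45 = 6.7 points
- k = 5: 5/45 = 11.1 points

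At a later time, suppose that a proportion q of the remaining patients has had an event (q is also assumed) and that the k patients are never seen to progress or die. EFS is then (1 − q) with censoring and (1 − q)(45 − k)/45 with event coding.

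| k | q = 0.20: censored → event | Difference | q = 0.30: censored → event | Difference |
|---|---|---|---|---|
| 1 | 80.0% → 78.2% | 1.8 | 70.0% → 68.4% | 1.6 |
| 3 | 80.0% → 74.7% | 5.3 | 70.0% → 65.3% | 4.7 |
| 5 | 80.0% → 71.1% | 8.9 | 70.0% → 62.2% | 7.8 |

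These are upper-end values for each k. Every patient of type (a) who is later observed to progress or die becomes an event under the censoring sentence too, which narrows the later gap.

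**The case against.** **Detail belongs in the SAP.** Section 5.2.1 provides for a statistical analysis plan, where full censoring rules commonly sit. That would answer a complaint that the protocol says too little. It does not answer this one, because the protocol states a rule and the rule disagrees with its own definition.

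**The event list is explicit, and the affected group is narrow.** A careful analyst might let the list prevail, and the trial enrols only disease judged resectable, so k may be small. Both points are fair. They limit the size of the problem but do not make the two sentences agree.

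**Failures are delayed, not lost.** This largely stands. Note 14 to the Study Flow Chart asks for continued imaging of patients who stop treatment for reasons other than progression, until progression, new anti-tumour therapy or death. Survival follow-up (note 20; section 4.7) records deaths. A reader might infer that the censoring rule removes these patients from EFS for good, but the documents do not support that in general. The limit is that note 14 ends the imaging once other anti-tumour therapy starts. From then on such a patient may stay censored unless a death, or a progression found by other means, is recorded.

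**Two stronger readings fail.**

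- A reader might infer that progression before surgery followed by resection can be scored two ways, because one limb of the definition requires inoperability while sections 3.6.1 and 3.6.2 permit surgery after progression. The text does not say this. RECIST progression is a separate, unconditional alternative and the earliest alternative counts, so this patient is an event at progression, and the censoring sentence agrees (row b).
- A reader might also see an error in the time origins, since EFS runs from enrolment while OS is "the time from study entry (i.e., after signing ICF) to death from any cause". The protocol does not define the enrolment date. Section 4.2 allows 28 days for screening, whereas the Study Flow Chart places consent at day −14 to −1, so the size of any gap is not established. No comparison of the two curves is planned.

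**Conclusion.** The point holds in a limited form: the rule is wrong as written. Under section 5.1.2, a living patient with an unresectable tumour and no RECIST progression is an EFS event by the definition. By the only censoring sentence offered, that patient is censored, or becomes an event at a later date. The bias is upward.

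Its size cannot be derived from the protocol. With k assumed and all 45 at risk, it is at most about 2.2 points (k = 1) to 11.1 points (k = 5) just after surgery, and smaller later to the extent that these patients progress or die under observation.

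The conclusion rests on applying the sentence to EFS, which its position in the EFS item implies, and on reading tumour progression in its ordinary sense. EFS is a secondary endpoint with no stated test or power, so the primary pCR analysis and the sample size do not change. The correction should be made, but it does not put the trial's main conclusion at risk.

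**What to change.** In section 5.1.2, replace the term progression-free survival with EFS, and state that EFS is censored at the last evaluable tumour assessment only for subjects with none of the listed EFS events, including unresectable tumour. Carry the same wording into the SAP.

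The cost is one sentence of protocol text. No new data, patients or visits are needed, and clinical management does not change. The reported EFS may be slightly less favourable if any such patients occur. No additional sensitivity analysis for progression followed by resection is required, because the definition already counts that progression.

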#### **3.5 Inclusion and exclusion criteria**

##### **3.5.1 Inclusion criteria**

Subjects must meet the following inclusion criteria:

- 1) Age  $\geq 18$  and  $\leq 75$  years with a ECOG PS score of 0-1;
- 2) Subjects who can adhere to the study protocol;
- 3) At least one measurable lesion according to RECIST 1.1 criteria;
- 4) Stage IIA, IIB, IIIA, and IIIB NSCLC with histologically or cytologically

confirmed resectable NSCLC according to International Association for the Study of Lung Cancer and the 8th edition lung cancer TNM staging of American Joint Committee on Cancer Staging;

5) Participants must have a tumor tissue sample available for PD-L1 immunohistochemistry (IHC) and must submit a formalin-fixed, paraffin-embedded (FFPE) tissue block or unstained tumor tissue section and corresponding pathology report prior to enrollment. Tissue must be biopsy specimens from hollow-needle aspiration biopsies, excisions, or incisions. Fine-needle aspiration biopsies obtained by EBUS are insufficient for biomarker review and as a basis for randomization.

6) Tumor tissue samples must be fresh or obtained within 3 months prior to enrollment.

7) For all suspicious mediastinal lymph nodes evaluated by PET-CT or contrast CT findings, a pathological diagnosis was not necessarily required.

8) Good hematopoietic function, defined as absolute neutrophil count  $\geq 1.5 \times 10^9/L$  (not receiving granulocyte colony-stimulating factor supportive therapy), platelet count  $\geq 100 \times 10^9/L$ , hemoglobin  $\geq 90$  g/L; (no transfusion or no erythropoietin dependence within 7 days);

9) Good liver function, defined as serum total bilirubin  $\leq 1.5$  times the upper limit of normal (ULN); glutamic oxaloacetic transaminase (AST) and glutamic pyruvic transaminase (ALT) levels  $\leq 2.5$  times ULN in patients without hepatic metastases; and AST and ALT levels  $\leq 5$  times ULN in patients with documented hepatic metastases;

10) Good renal function, defined as serum creatinine  $\leq 1.5$  times ULN or calculated creatinine clearance  $\geq 60$  ml/min (Cockcroft-Gault formula); urine protein less than 2+ on routine urinalysis, or 24-h urine protein  $< 1$  g;

11) Good coagulation function, defined as an international normalized ratio (INR) or prothrombin time (PT)  $\leq 1.5$  times ULN;

12) Total lung function (e.g., FVC, FEV1, TLC, FRC, and DLco) capable of tolerating the proposed lung resection, as assessed by the surgeon;

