## **6. Adverse event reporting**

### **6.1 Adverse event observation**

An adverse event (AE) is any unfavorable medical occurrence that happens after a subject in a clinical trial has signed an informed consent form, regardless of whether it is causally related to the treatment. AEs can encompass a wide range of unfavorable symptoms, signs, laboratory test abnormalities, or diseases. Specifically, AEs include at least the following:

- 1) A pre-existing medical condition or disease is recorded as an AE only if it worsens after the initiation of study treatment.

2) Any newly occurring AE: This includes any new adverse medical condition (such as symptoms, signs, or newly diagnosed diseases).

3) Abnormal clinically significant laboratory test results that are not attributable to concomitant diseases.

Adverse events that occur during both the pre-treatment and post-treatment phases are also considered AEs according to regulations. Therefore, safety monitoring for AEs or serious adverse events (SAEs) should be reported from the time the subject enters the trial (by signing the informed consent form) until the end-of-trial visit.

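### OS and EFS are given different starting points, so the same death can carry an OS time up to 28 days longer than its EFS time

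*Protocol*

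**What the plan says.** OS and EFS are both secondary endpoints (section 3.3), defined in neighbouring entries of section 5.1.2.

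- **OS:** "Overall survival (OS), defined as the time from study entry (i.e., after signing ICF) to death from any cause".
- **EFS:** "Event-free survival (EFS), defined as the interval from enrolment to the" first of several events. Death is among them: "as assessed by the investigator; or death from any cause".

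Other sections bear on what the two starting points mean.

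- **Section 6.1** sets the adverse event reporting window as running "from the time the subject enters the trial (by signing the informed consent form) until the end-of-trial visit". Entry and consent are equated there too.
- **Section 4.2** has consent signed when screening opens: "patients will be asked to read and sign the informed consent form before undergoing any procedures related to the study". The rule concerns procedures outside standard care. Eligibility tests follow, and "The screening period for this study will be completed within 28 days".
- **Section 3.5.1, criterion 5** requires a tissue block or "unstained tumor tissue section and corresponding pathology report prior to enrollment".
- **The study flow chart** puts consent in the column for day -14 to day -1, and verification of the enrolment criteria in the column for day -7 to day -1.

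The protocol does not say which date counts as enrolment. It names no analysis set for OS, and it states no test or threshold for OS or EFS.

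**The concern.** Death from any cause ends both endpoints. On a common clock, a patient whose first event is death has the same OS and EFS time. With one clock starting at consent and the other at enrolment, the two times differ by however long screening took after consent. That length varies between patients for logistical reasons, such as a new biopsy when no tissue is available.

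Three things are at stake, all modest:

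- The EFS and OS curves do not share a time axis, so their landmark rates refer to different moments.
- The interval from an EFS event to death, obtained by subtracting EFS from OS, absorbs the consent-to-enrolment gap.
- If OS is reported in enrolled patients, survival to enrolment is a condition of being counted. The pre-enrolment days then add survival time without risk, and the shift goes in one direction only.

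This is not a detail left open for an SAP. The protocol fixes both origins, and fixes them differently.

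**Working it through.** **1. The plan's own figures.** The protocol gives no figure for OS or EFS. Its only computed figure is the two-stage design for pCR in section 5.3. With pCR rates of 25% and 45%, and the printed 80% read as power, stopping at 5 or fewer of 17 and requiring more than 14 of 41 overall (a cut-off the protocol does not print) gives a type I error of 0.0498 and power of 0.803. So 41 patients and the stage 1 rule reproduce. Neither uses a time origin, so nothing below changes them.

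**2. Are the two origins the same point?**

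| Step | Where it is placed | Source |
|---|---|---|
| Entry to the trial | At signing of consent | Section 6.1, and the gloss in the OS definition |
| Consent | Start of screening, before study procedures | Section 4.2 |
| Tissue and pathology report | Before enrolment | Section 3.5.1, criterion 5 |
| Verification of enrolment criteria | Day -7 to day -1 | Flow chart |

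Consent opens screening, and enrolment follows once the requirements are met. They are separate steps, and enrolment is normally the later one.

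**3. Size of the gap.** Let g be the days from consent to enrolment. The flow chart bounds g at about 0 to 14 days, and section 4.2 at 0 to 28 days. For a patient whose first event is death, OS - EFS = g. Using 30.4375 days per month:

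- 7 / 30.4375 = 0.23 months
- 14 / 30.4375 = 0.46 months
- 28 / 30.4375 = 0.92 months

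Example: consent on day -28, enrolment on day 0, death on day 200 with no earlier event. EFS is 200 days and OS is 200 + 28 = 228 days.

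**4. Effect on landmark OS rates.** Three assumptions are made because the protocol gives no figures: OS is analysed in enrolled patients; the death hazard h is constant from enrolment at 0.08, 0.15 or 0.25 per year; and every patient has the same gap d (g in years). A hazard of 0.08 means 1 - exp(-0.08) = 7.7% die in the first year, and 0.25 means 1 - exp(-0.25) = 22.1%. Starting the clock at consent raises the rate read at L years by

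exp(-h(L - d)) - exp(-hL).

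For h = 0.15, L = 1 and 28 days (d = 0.0767): exp(-0.15 × 0.9233) - exp(-0.15) = 0.8707 - 0.8607 = 0.0100, or 1.00 point.

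| Landmark | Gap | h = 0.08 | h = 0.15 | h = 0.25 |
|---|---|---|---|---|
| 1 year | 14 days | 0.28 | 0.50 | 0.75 |
| 1 year | 28 days | 0.57 | 1.00 | 1.51 |
| 2 years | 14 days | 0.26 | 0.43 | 0.58 |
| 2 years | 28 days | 0.52 | 0.86 | 1.17 |

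(Entries are percentage points.) With a common gap, median OS moves by the gap itself, so by at most 0.92 months.

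**5. Cross-check on another scale.** Assume instead a 24-month OS from enrolment of 70%, 80% or 90%. The overstatement at 24 months is then 0.24, 0.17 or 0.09 points for 7 days; 0.48, 0.34 or 0.18 for 14 days; and 0.96, 0.69 or 0.36 for 28 days. The direction and order of size agree.

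**The case against.** The strongest reply is that the OS wording says only that entry comes after the consent signature. That sets an order and fixes no date. Enrolment also comes after consent and is itself undated, so the authors may have meant one point. The equation of entry with consent in section 6.1 serves the adverse event window, not OS. This stands as a caution: reading the OS origin as consent is an inference. It is still the better-supported reading, because the OS definition and section 6.1 use the same gloss. If one point was meant, the text should name it.

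A reader might infer that every OS time contains screening days. The protocol does not establish this. The flow chart windows for consent and for verification of the enrolment criteria overlap, so both can fall on one day and the gap can be zero. The flow chart notes also accept imaging obtained before consent, which can shorten the interval. The 28 days is a ceiling for the whole screening period.

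A reader might also infer that the OS results will be biased and the landmark rates wrong. That goes too far. Survival from a declared origin is a legitimate quantity, and the argument about risk-free days holds only if OS is analysed in enrolled patients. That is the natural reading for a trial that counts enrolled patients, but the protocol does not say so. If OS covered everyone who consented, those days would carry risk, but OS and EFS would then rest on different patients.

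Finally, the effect is small against sampling error. With 45 patients and an assumed OS of 80%, the 95% half-width is about 1.96 × sqrt(0.8 × 0.2 / 45) = 11.7 points. This stands, and it is why the point is minor.

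**Conclusion.** The point holds as a minor inconsistency. The protocol gives its two survival endpoints different, imprecisely dated starting points. Where enrolment is later than consent, a death without an earlier EFS event has an OS time 0 to 28 days longer than its EFS time (0 to 14 days by the flow chart).

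If OS is reported in enrolled patients, the shift is upward only. It is about 0.3 to 0.8 points at 1 year when everyone has a 14-day gap, and 0.6 to 1.5 points when everyone has a 28-day gap. These are upper-end figures, since real gaps will vary and some may be zero. They rest on the assumed hazards of 0.08 to 0.25 per year.

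No decision in the protocol turns on the difference: the study has one arm, and the sample size and stage 1 rule concern pCR alone. The reason to act is that the conflict is written into the definitions and costs almost nothing to remove.

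**What to change.** In the OS entry of section 5.1.2, replace the phrase that makes study entry the origin and glosses it by the consent signature with the single word enrolment, which EFS already uses.

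That alone would move OS onto an undated origin, so add one sentence stating which recorded date counts as enrolment. Verification of the enrolment criteria, already a step in the flow chart, is one candidate. The protocol does not list an enrolment date as a data item, so check that the case report form captures the chosen date.

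State that both OS and EFS are measured from that date in the same enrolled patients. The adverse event window in section 6.1 can keep its start at consent.

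The cost is one phrase and a sentence or two of text, and at most one date field. OS may become marginally less favourable, by no more than the amounts shown above under those assumptions.
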